**Fig. 2 Fig2:**
[figure not shown]
Conceptual framework reflecting the outcome measures and their effects on the continuum of care. Note: The framework outlines the relationship between the outcome measures (boxed in dotted line) and the HIV continuum of care (blue). The right-most panel (orange) represents the outcome measures in the context of the socioecological levels of influence

We will also assess secondary outcomes, including (i) the impact of CAD on the work burden of healthcare providers at the ART sites, (ii) cost-effectiveness of this model and its impact on (iii) the quality of life, (iv) mental health, (v) social support, and (vi) stigma and discrimination faced by people living with HIV in the community. We will report the time and volume of stable people living with HIV seen at the ART sites as a measure of the workload of healthcare providers in HIV care delivery. We will present quality of life, mental health, social support, stigma and discrimination, and workload (burnout) as scores measured using validated tools described in the section below. We will perform an economic evaluation to determine if the intervention is cost-effective. We will also determine the acceptability, feasibility, barriers, and facilitators to implementing the CAD model in Cambodia using the qualitative method.

### Data collection

All people living with HIV will be interviewed face-to-face by trained data collection teams using structured questionnaires. We will interview all participants in the intervention and control arms at baseline (0 months), midline (at 12 months of the intervention), and endline (at 24 months of the intervention). We will collect qualitative data in private locations using semi-structured interview guides. The data collection timelines for quantitative surveys and qualitative in-depth interviews and focus group discussions are illustrated in Fig. 3.

**Fig. 3 Fig3:**
[figure not shown]
Timelines and data collection activities for the quasi-experimental study to evaluate the community ART model

### Variables and measurements

We will collect information on sociodemographic (age, sex at birth and gender, membership of key population groups, income, residence, education, family, and dependency) and HIV treatment history and health status (duration of taking ART, transportation mode, relationship, and satisfaction with health care workers). We will adapt questionnaires previously implemented by NCHADS to measure medication adherence and retention in care and treatment [28, 29]. Viral load will be obtained from medical records at the attached ART clinics.

We will measure depressive symptoms using the Center for Epidemiologic Studies Depression Scale (CES-D) [30], quality of life using the WHO Quality of Life BREF (WHOQOL-BREF) for people living with HIV and EQ-5D-5L [31–33] and stigma and discrimination using the People Living with HIV Stigma Index [18]. We will also measure self-efficacy and levels of social support using the Perceived Self-Efficacy for Receiving Antiretroviral Therapy Scale (PSEARTS) [34–36] and Berlin Social Support Scale (BSSS) [35, 37, 38], respectively. For the economic evaluation, we will collect direct and indirect costs for follow-up care and ARV refills. We will assess healthcare providers’ workload at ART clinics using two different measures. First, we will evaluate health providers' workload and burnout using the NASA Task Load Index [39] and a single-item measure of burnout adapted from the Physician Worklife Study [40–43], respectively. Second, we will measure the number of people living with HIV (both stable and unstable) served per day and week and the time spent per people living with HIV at the different service points in the clinic. For the qualitative assessment, we will explore the perception of people living with HIV, HIV service providers, and other key stakeholders on the advantages and disadvantages, acceptability, feasibility, and sustainability of CAD in the HIV continuum of care.

### Data management

We will collect and manage data using REDCap [44, 45]. Data coding, quality control, and data entry will be done. We will enter all data into the database within 1 week of collection. Subsequently, we will export the database into Microsoft Excel (Microsoft Corp., Redmond, Washington, USA) to check for consistency periodically. All questionnaires will be checked for errors by the team leaders, and necessary corrections will be made before data entry and analyses.

### Data analyses

We will compare the characteristics of the participants in the intervention and control arms using descriptive statistics. In the presence of significant differences, we will adjust for them in the subsequent between-group (i.e., intervention vs. control) analyses. Key outcome indicators will be compared using inferential statistics such as Chi-square tests for categorical variables and Student’s *t*-test for continuous variables. To evaluate the effectiveness of the CAD model intervention, we will compare the outcome indicators at baseline, midline, and endline within and between the intervention and control arm using the difference-in-differences method [46]. We will apply multivariable regression analyses using mixed models, logistic and Cox regression, considering repeated measurements design and the nature of the response variables. Statistical analyses will be performed in STATA (Stata Corp LP, Texas, United States of America) and R (R Foundation for Statistical Computing, Vienna, Austria). For qualitative data, we will transcribe audio recordings verbatim, and the transcripts will be coded using NVIVO (QSR International). Content analyses will be performed to identify emerging categories, themes, and common and divergent patterns pertinent to the study’s objectives.

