### Settings

This study will include 10 ART clinics in Phnom Penh capital city and four provinces (Kampong Thom, Kampot, Koh Kong, and Takeo) for the intervention arm (Table 1). We will include 10 other ART clinics in Phnom Penh and five provinces (Kampong Cham, Pailin, Preah Sihanouk, Siem Reap, and Prey Veng) for the MMD control arm (Table 1). These sites have been purposively selected based on (i) the availability of implementing partners (Cambodian People Living with HIV Network, ARV User Association, and Partner in Compassion), (ii) the number of eligible people living with HIV for enrollment in the intervention and control arms, and (iv) advice from the national HIV program on the accessibility of the clinics.

**Table 1 Tab1:** Study sites for the quasi-experimental study to evaluate the CAD model

Intervention sites			Control sites		
Province	ART clinic	Setting	Province	ART clinic	Setting
Kampot	Kampot Hospital	Urban	Kampong Cham	Kampong Cham Hospital	Urban
Kampot	Kampong Trach Hospital	Rural	Kampong Cham	Cheung Prey Hospital	Rural
Koh Kong	Smach Meanchey Hospital	Urban	Pailin	Pailin Hospital	Urban
Koh Kong	Sre Ambil Hospital	Rural	Preah Sihanouk	Preach Sihanouk Hospital	Urban
Phnom Penh	Mean Chey Hospital	Urban	Phnom Penh	Chhouk Sar I Clinic	Urban
Phnom Penh	Pochintong Hospital	Urban	Phnom Penh	Sam Dach Ov Hospital	Urban
Kampong Thom	Kampong Thom Hospital	Urban	Siem Reap	Siem Reap Hospital	Urban
Kampong Thom	Baray Santok Hospital	Rural	Siem Reap	Soth Nikum Hospital	Rural
Takeo	Takeo Hospital	Urban	Prey Veng	Prey Veng Hospital	Urban
Takeo	Kirivong Hospital	Rural	Prey Veng	Neak Loeung Hospital	Rural

*ART* antiretroviral therapy, *CAD* community ART delivery

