### Sample size calculation

A target sample size of approximately 2000 stable people living with HIV is required to provide at least 80% power to detect a 10% relative difference retention in care or maintenance of viral suppression. The sample size calculation was based on 10% attrition and conservative estimates of retention in care or viral-suppression maintenance: 50 and 55% maintenance of viral suppression in the MMD (control arm) and CAD (intervention arm), respectively. Findings from a recent randomized controlled trial in high- and medium-HIV-prevalence settings of people living with HIV with detectable viral load showed that CAD increased viral suppression compared to the control group (74% vs. 63%, RR 1.18, 95% CI 1.07–1.29). Under similar scenarios, our proposed study’s power with 2000 participants in each arm will be at least 90%.

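### Clinic determines the arm, but neither the stated analysis nor the sample size says how between-clinic variation is handled

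*Protocol article*

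**What the plan says.** Settings fixes the arm by clinic. For CAD, "This study will include 10 ART clinics in Phnom Penh capital city and four provinces"; for MMD, "We will include 10 other ART clinics in Phnom Penh and five provinces". Assignment was not random: "These sites have been purposively selected based on" partner availability, numbers of eligible patients and advice on accessibility. Table 1 lists no clinic in both arms.

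Data analyses states: "Key outcome indicators will be compared using inferential statistics such as Chi-square tests for categorical variables", with Student's t-test for continuous variables. It then assigns the evaluation of effectiveness to difference-in-differences over baseline, midline and endline, and adds mixed, logistic and Cox regression "considering repeated measurements design and the nature of the response variables". It does not say which random effects the mixed models contain.

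Sample size calculation states: "A target sample size of approximately 2000 stable people living with HIV is required to provide at least 80% power", on the basis of "50 and 55% maintenance of viral suppression in the MMD (control arm) and CAD (intervention arm), respectively", with 10% attrition. For a second scenario it says the "power with 2000 participants in each arm will be at least 90" percent.

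Clinic, clustering, an ICC, a design effect and cluster-robust variance appear in neither section. The limitations given in the Discussion are lack of randomisation, contamination and information bias.

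**The concern.** When all participants of a clinic are in the same arm, any difference between clinics that is unrelated to CAD goes straight into the arm contrast. Chi-square and t-tests treat participants as independent and do not see this source of error. A model that allows only for repeated measures on a person does not see it either.

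The protocol itself gives reasons to expect clinic variation. The MMD refill interval is left to each clinic. Community workers are attached to a clinic and run group sessions. Viral load is taken from each clinic's records. Sites are both urban and rural.

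At stake are the standard errors of the between-arm estimates for the three primary outcomes and the participant-level secondary outcomes. If they are too small, chance differences between two sets of 10 clinics may be reported as effects of CAD, in a study meant to inform scale-up.

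**Working it through.** **Inputs from the protocol.** 10 clinics per arm; 2000 participants per arm; 10% attrition; 50% vs 55%. Average clinic size is 2000/10 = 200, or 180 evaluable.

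**Assumptions.** Two-sided 5% test (not stated in the article); 2000 read as per arm; equal clinic sizes; ICC from 0.001 to 0.05.

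**1. The protocol's own figure.** With independent participants,
n = [1.96·√(2·0.525·0.475) + 0.842·√(0.50·0.50 + 0.55·0.45)]² / 0.05² = 1565 per arm, and 1565/0.9 = 1739 with attrition.
With 1800 evaluable per arm the power is 85%, so at least 80% is met. At 63% vs 74% it exceeds 99.9%, so at least 90% is met. Both results use no design effect, so the stated power holds as computed only if participants within a clinic are independent.

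**2. A between-arm participant-level chi-square test.** Design effect DEFF = 1 + (180 − 1)·ICC. Actual type I error = 2·[1 − Φ(1.96/√DEFF)]. Power for 50% vs 55% uses an effective size of 1800/DEFF per arm.

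| ICC (assumed) | DEFF | √DEFF | Type I error | Power, 50% vs 55% |
|---|---|---|---|---|
| 0.001 | 1.18 | 1.09 | 7.1% | 79% |
| 0.005 | 1.90 | 1.38 | 15.5% | 59% |
| 0.01 | 2.79 | 1.67 | 24.1% | 44% |
| 0.02 | 4.58 | 2.14 | 36.0% | 29% |
| 0.05 | 9.95 | 3.15 | 53.4% | 16% |

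√DEFF is the factor by which the naive confidence interval is too narrow. The type I error reaches 10% at an ICC of about 0.002.

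A beta-binomial simulation (40,000 replicates, 10 clinics per arm, event rates 50% and 90%) agrees within about 0.5 points. A t-test on clinic means with 20 − 2 = 18 degrees of freedom held 4.6–5.3% throughout. With unequal clinic sizes (assumed coefficient of variation 0.6, event rate 90%) the chi-square error rises to 19%, 28% and 58% at ICC 0.005, 0.01 and 0.05.

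**3. Difference-in-differences.** Let c be the correlation over time of a clinic's effect (clinic autocorrelation) and r the within-person correlation. The ICC of the change score is
ICC·(1 − c) / [ICC·(1 − c) + (1 − ICC)·(1 − r)].
At ICC 0.01, c = 0.8, r = 0 this is 0.002/(0.002 + 0.99) = 0.0020, so DEFF = 1 + 179·0.0020 = 1.36 and the type I error is 9%. At r = 0.5 it is 0.002/(0.002 + 0.495) = 0.0040, DEFF = 1.72, and the error is about 14%.

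| ICC | c | Type I error, r from 0 to 0.5 |
|---|---|---|
| 0.01 | 0.8 | 9–14% |
| 0.01 | 0.5 | 16–24% |
| 0.05 | 0.8 | 25–37% |
| any | 1.0 | 5% |

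**4. Where differencing helps.** Everyone is in care at enrolment, so retention has no baseline clinic variation to subtract. A Cox model for retention has one event time per person, so handling repeated measures gives it no protection. Suppression is probably similar, because eligibility selects for treatment success. The criterion is not purely virological, however, since it also allows a CD4 count. For adherence and scale scores, clinic differences may persist over time, and the relief could be substantial.

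**The case against.** The strongest reply is that the article does not clearly plan the chi-square test as the between-arm effect test. The Methods part of the Abstract uses descriptive and inferential statistics for comparisons within each arm, and difference-in-differences for the comparison between arms. In Data analyses, the sentence with the chi-square test names no arms, although the sentence before it concerns between-group analyses. This stands as an ambiguity. The figures of 7% to 53% apply only if that test is used between arms, and under difference-in-differences the inflation is generally smaller.

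A reader might infer that the false-positive rate is several times 5% as a matter of fact. The documents do not support that, because they give no ICC. At 0.001 the chi-square error is about 1.4 times nominal; it reaches three times nominal only at about 0.005.

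A reader might also infer that the models exclude clinic. They do not say so. Mixed models are named without their random effects, and a clinic effect is unstated rather than ruled out. The choice of random effects and of a degrees-of-freedom correction is often left to an analysis plan.

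That last argument does not remove the point. The article names tests that assume independence, names repeated measurement as the only dependence, and gives a sample size computed as if participants were independent. A clinic term in the mixed models would not repair the chi-square and t-tests.

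For provider outcomes, the figures for 180 patients per clinic do not carry over. Staff per clinic is not given, so no size can be computed.

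**Conclusion.** The point holds in a limited form. Clinic is the unit of assignment, and neither the analysis text nor the sample size states any allowance for between-clinic variation. Followed as written, the plan gives standard errors that are too small wherever clinics differ or drift apart.

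The size depends on assumptions that the protocol does not supply. A between-arm chi-square test at nominal 5% runs at about 7%, 15%, 24% and 53% for ICC 0.001, 0.005, 0.01 and 0.05. Difference-in-differences runs at about 9–14% for ICC 0.01 and clinic autocorrelation 0.8, and at 5% if clinic differences are perfectly stable. The chi-square figures are the better guide for retention, and probably for suppression.

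**What to change.** State in Data analyses that every between-arm estimate accounts for clinic, including the difference-in-differences term and the Cox model. Either of two routes will do:

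- **Model-based.** Use a clinic random effect, with participant within clinic and a clinic-by-period term for repeated measures, or clinic-clustered variance. Add a small-sample correction suited to 20 clusters. A clinic intercept alone is not enough for difference-in-differences, because it absorbs only the stable clinic differences that differencing already removes.
- **Clinic-level.** Analyse clinic summaries, or clinic changes from baseline, on about 18 degrees of freedom.

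Say that participant-level chi-square and t-tests will not serve as between-arm effect tests. Restate the power under an assumed range of ICC, so that readers can see what 20 clinics can detect.

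The cost is a changed model specification and wider confidence intervals: by the √DEFF factors above for a single-time comparison, and by less where differencing helps. No new data are needed. The change corrects the standard errors; it does not remove confounding from purposive site selection.

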## Background

Cambodia has substantially reduced the prevalence of human immunodeficiency virus (HIV) in the general adult population aged 15–49 years from 1.7% in 1998 to 0.5% in 2019 [1, 2]. Cambodia is also one of the three countries in the Asia-Pacific region to have achieved the UNAIDS 90–90-90 targets. More than 90% of people living with HIV receiving antiretroviral therapy (ART), and 80% had viral suppression [3]. Despite the successes, there are persistent concerns regarding attrition from HIV testing and linkages to care and the retention in care, especially among members of the hidden populations in Cambodia [4]. A recent systematic review and meta-analysis of studies in low- and middle-income countries reported that groups with vulnerable socioeconomic and clinical status and social support were at increased risk of loss to follow-up from ART programs [5]. From the health systems perspective, care providence at a higher level was associated with a higher risk of attrition from the treatment cascade [5]. Therefore, through decentralization of care and community involvement, differentiated ART delivery models that are contextualized could improve care retention and sustain treatment outcomes [6, 7].

In Cambodia, ART is primarily administered at 68 public ART clinics across 25 provinces [8]. Clinics operated by several non-governmental organizations (NGOs) also complement the ART services. However, regular clinic runs and ARV refills posed a heavy resource burden on people living with HIV to remain optimally engaged in care [9]. Besides, it also contributed significant workload on the health facilities and service providers to meet the demands of both stable people living with HIV and unstable people living with HIV, who required more frequent follow-ups [10]. Hence, a differentiated care model would enable health providers to invest more time on unstable and complicated cases, thus improving overall service quality [10]. An appointment-spacing and multi-month dispensing (MMD) model has been introduced to all ART clinics to increase service efficiency and decrease congestion by reducing clinical visits and refill appointments for stable people living with HIV [11]. However, concerns regarding sub-optimal storage of antiretrovirals (ARVs), poor adherence, and missed appointments have emerged [12].

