### Participants

We define stable people living with HIV as individuals who (i) are ≥15 years, (ii) have received first-line ART for at least 1 year, (iii) did not report ART-related adverse reactions or drug interactions requiring regular monitoring; (iv) do not have tuberculosis (presumptive/confirmed), other opportunistic infections, and are not taking any prophylactic treatment; (v) are not pregnant or breastfeeding (for women); (vi) have a good understanding of lifelong treatment and adherence to medication; and (vii) have achieved treatment success—two consecutive undetectable viral load and/or CD4 counts above 200 cells/mm^3^ [11, 19, 28]. We will conduct in-depth interviews and focus group discussions with people living with HIV, representatives of the communities, government officials at different levels (community, health centers, operational districts, provincial health departments, and national programs), local and international NGOs, donors and other developmental partners in Cambodia to explore the acceptability, barriers, and facilitators to implementing the CAD model.

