### Outcome measures

We present the conceptual framework reflecting the outcome measures and their effects on the continuum of care in Fig. 2. Our primary outcomes will include (i) viral load suppression, (ii) retention in care, and (iii) adherence to ART. Viral load suppression is defined as at least 90% of the study participants in the intervention arm will have a viral load of < 1000 RNA copies/mL at the end of the intervention period. We define care retention as the proportion of people living with HIV who will remain in HIV care and treatment 12 and 24 months after study commencement. Treatment adherence will be self-reported, and we will present the proportion of people living with HIV with good adherence to ART based on standard cut-offs.

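### For retention, difference-in-differences is only the endline difference between arms, and for viral suppression it probably removes little confounding, because eligibility fixes or nearly fixes the baseline

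*Protocol article*

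**What the plan says.** The study is not randomised. Twenty clinics, 10 per arm, were chosen purposively (Settings). The Data analyses section names one method for evaluating effectiveness: "we will compare the outcome indicators at baseline, midline, and endline within and between the intervention and control arm using the difference-in-differences method". The abstract repeats this for differences between arms. Neither place exempts a primary outcome.

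Three definitions bear on this:

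- Retention (Outcome measures) is "the proportion of people living with HIV who will remain in HIV care and treatment 12 and 24 months after study commencement".
- Viral suppression (Outcome measures) is judged on participants who "will have a viral load of < 1000 RNA copies/mL at the end of the intervention period".
- Eligibility (Participants) requires that people "have received first-line ART for at least 1 year" and have reached treatment success, given as "two consecutive undetectable viral load and/or CD4 counts above 200" cells/mm³.

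The Sample size calculation speaks of maintaining suppression, so the authors also expect participants to start suppressed. The Data analyses section further plans adjustment for baseline characteristics that differ significantly between arms, and mixed, logistic and Cox models. The Discussion accepts that unmeasured and residual confounding cannot be fully dealt with.

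**The concern.** Difference-in-differences guards against stable differences between non-randomised groups because such differences show in the outcome before the intervention starts and can be subtracted. If eligibility forces the baseline outcome to the same value in both arms, those differences are hidden at month 0 and appear only during follow-up. The subtraction then removes nothing.

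This matters because sites were picked partly on the presence of implementing partners and on clinic accessibility, both of which could plausibly relate to attrition. Apart from Phnom Penh, the arms share no province (Table 1). A reader who sees difference-in-differences named as the effectiveness method would credit the retention result, and largely the suppression result, with protection that it does not have.

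**Working it through.** **The plan's own figure.** The protocol gives no number on this point. Its sample size is not in dispute. For 50% vs 55%, two-sided 5% (assumed; alpha is not stated) and 80% power, 1,565 per arm are needed, or 1,565/0.9 = 1,739 after 10% attrition. With 2,000 enrolled and 1,800 evaluable, power is 85.2%, so the claim of at least 80% stands.

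**Retention.** Let E and C be the proportions in care in the intervention and control arms.

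- DiD = (E24 − E0) − (C24 − C0).
- Anyone enrolled has been on ART for at least a year and is recruited from the clinic, so E0 = C0 = 100%.
- Hence DiD = E24 − C24, exactly.

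Example with no true effect, where site differences alone give 95% vs 92% at 24 months: DiD = (95 − 100) − (92 − 100) = +3 points, and the raw difference is 95 − 92 = +3 points. A site difference of 1 or 5 points would likewise pass through whole.

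For scale, assume a 95% control rate, 1,800 per arm in 10 clinics (180 each), 18 df and 80% power. The detectable difference d solves d = (2.101 + 0.862) × √{[0.95×0.05 + (0.95+d)(0.05−d)] × DE/1,800}, with DE = 1 + 179 × ICC.

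| Assumed ICC | DE | Detectable d |
|---|---|---|
| 0 | 1.00 | 1.9 points |
| 0.01 | 2.79 | 3.0 points |
| 0.02 | 4.58 | 3.7 points |

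So a site difference of a few points is as large as the effect that the study could detect. The 95%, the ICCs and the 3-point site difference are illustrations, not figures from the protocol.

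**Viral suppression: how close to the ceiling?** The outcome threshold (<1000 copies/mL) is looser than undetectable, so anyone admitted on viral load starts suppressed. Only those admitted on CD4 alone can start unsuppressed. If a share f enters that way and a proportion s of them is suppressed, baseline suppression is 1 − f(1 − s). The article does not give f or s. Its Background reports for Cambodia "and 80% had viral suppression", used here as the low end for s, with 95% as the high end.

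| f (assumed) | s = 80% | s = 95% |
|---|---|---|
| 10% | 98.0% | 99.5% |
| 20% | 96.0% | 99.0% |
| 50% | 90.0% | 97.5% |

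**Viral suppression: how much bias is removed?** A simulation set the treatment effect to zero and gave the intervention arm a better unmeasured prognostic factor (normal, SD 1, mean shift 0.5 on the logit scale, intercept 2.0). Suppression at the two visits was independent given that factor. Share removed = (raw bias − DiD bias)/raw bias.

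| Candidates not selected on viral load | Raw 24-month bias | DiD bias | Removed |
|---|---|---|---|
| 0% | 4.15 points | 4.15 points | 0% |
| 10% | 4.29 | 3.69 | 0.60/4.29 = 14% |
| 30% | 4.52 | 2.70 | 1.82/4.52 = 40% |
| 100% | 5.03 | 0.02 | essentially all |

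These are shares of candidates. Among control-arm enrollees, where 84.4% of candidates are suppressed, 10% becomes 0.1/(0.1 + 0.9×0.844) = 11.6%, and 30% becomes 0.3/(0.3 + 0.7×0.844) = 33.7%. The last row shows that the method works when baseline is free to vary, as it is for adherence and the scale scores.

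**The case against.** A reader might infer that difference-in-differences gives no protection for two of the three primary outcomes. The documents support that only for retention. The and/or in the eligibility rule can admit people without documented suppression, so baseline suppression is not fixed, and part of the bias can be removed.

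A reader might also infer that a logistic difference-in-differences model would break down because the baseline log-odds are infinite. That requires no baseline failures at all and a time-by-arm interaction on the logit scale. The eligibility rule does not ensure the first, and the article does not specify the second for these outcomes.

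Nor do the documents show that clinic differences will inevitably be reported as the intervention effect. The plan has covariate adjustment and multivariable models, and Cox regression needs no baseline outcome value. Which model serves which outcome is detail that an article may leave to the full protocol or analysis plan. The Discussion also discloses residual confounding. And for retention, difference-in-differences is redundant rather than harmful: it gives the same number as the endline comparison.

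All of this stands, and it lowers the severity. It does not remove the point. The planned models reach measured factors only, and the only stated trigger for adjustment is a significant difference between arms, which is a poor guide to confounding. The variables listed under Variables and measurements include no earlier clinic-level rate of retention or suppression. The Discussion's caveat is general and does not say that the named method does nothing for retention. There is also only one wave before the intervention, so trends cannot be checked; that is a limit of the design, not an error.

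**Conclusion.** The point holds in two parts of different strength. For retention it is exact and needs no assumption beyond everyone being in care at entry: 0% of a pre-existing clinic difference is removed. For viral suppression it is probable, not certain: baseline is near the ceiling, and only a minor part of the bias is removed (about 14% to 40% when 10% to 30% of candidates are not selected on viral load). Those percentages depend on the simulation's assumed prognostic factor and on an admission share that the article does not state. Adherence and the scale scores are not affected. This should be fixed. It concerns what the analysis can be claimed to control, and the planned comparison of arms can still be made.

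**What to change.** - Keep difference-in-differences for adherence and the scale scores.
- For retention and suppression, state that the effect estimate is the 24-month between-arm difference, or a Cox model for retention, adjusted for covariates fixed in advance and not chosen by significance.
- Do not present difference-in-differences as confounding control for retention. For suppression, report how many participants were admitted on CD4 alone, so that readers can judge how far baseline was free to vary.
- Where clinic or NCHADS records allow, add each clinic's pre-study retention and its proportion below 1000 copies/mL, either as a clinic-level covariate or as the pre-period of a clinic-level difference-in-differences. Two or more earlier periods would also let trends be checked.

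The first three changes cost only wording and one extra tabulation. The last costs one data extraction. The article shows that viral load comes from clinic records and that the NCHADS data unit is involved in listing clinics, but not that historical series exist, so availability must be confirmed first.
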